### 5.4.3. Study Completion

A subject will be considered as completing the study if they meet any of the following criteria:

- Subject dies and a date of death is available.
- Subject is known to have died; however, the date of death cannot be obtained. (NOTE: Every effort must be made to obtain the date of death.)
- Subject has discontinued study treatment and has withdrawn consent for collection of follow-up anticancer and survival data.

# 6. STUDY ASSESSMENTS

## 6.1. Screening

The screening period is the interval between signing the ICF and the day the subject is

randomized in the study (Day 1). The screening period may not exceed 2 days. Informed consent must be obtained before performing any study-specific procedures that are not considered standard of care. Assessments that are required to demonstrate eligibility may be performed over the course of 1 or more days during this period.

Procedures conducted as part of the subject's routine clinical management (eg, complete blood count) and obtained before signing of informed consent may be used for screening or baseline purposes, provided that the procedure meets the Protocol-defined criteria and has been performed in the timeframe of the study. Results from the screening visit evaluations will be reviewed to confirm subject eligibility before randomization or the administration of study drug. Tests with results that fail eligibility requirements may be repeated once during the screening period if the investigator believes the results to be in error or believes there has been a change in eligibility status (eg, following recovery from an infection). For screening assessments that are repeated, the most recent available result before randomization will be used to determine subject eligibility. Treatment should start as soon as possible but within 1 days after the date of randomization.

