## 4.4. Randomization

The eligibility of patients is determined by study site staff. Then, the participants who meet the enrollment criteria will be randomized to receive one of the two treatments in a 1:1 ratio and stratified by disease status before transplantation (complete remission vs. non- complete-remission) and risk of acute GVHD (intermediate-risk vs. high-risk). Stratified permuted block randomization lists will be used to generate the stratified randomization. Randomization is implemented through an interactive web-based response system independent of study site staff and investigators. The codes are generated independently of the study by a statistician. The next assignment in the random sequence remained concealed because the treatment was assigned remotely. Treatment allocations are not masked to investigators or participants as CSA and methylprednisolone dosage are different between the two groups. The study staff who conducted the data analysis and assessments of outcomes will be masked for treatment allocations.

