### 5.4.1. Withdrawal Criteria

Subjects must be withdrawn from study treatment for the following reasons:

- The subject has experienced an unacceptable toxicity.
- Relapse of underlying malignancy.
- The subject is unable to tolerate ruxolitinib at a dose of 5 mg QD.
- Additional systemic therapy is required for GVHD progression or lack of response, including corticosteroid doses greater than those used on Study Day 1.
- Further participation would be injurious to the subject's health or well-being, in the investigator's medical judgment.
- The subject becomes pregnant.
- Consent is withdrawn.
- The study is terminated by the sponsor.

A subject **may** be withdrawn from study treatment as follows:

- If, during the course of the study, a subject is found not to have met eligibility criteria, then the medical monitor, in collaboration with the investigator, will determine whether the subject should be withdrawn from the study.
- If a subject is noncompliant with study procedures or study drug administration in the investigator's opinion, the sponsor should be consulted for instruction on handling the subject.

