## 6.2. Treatment

The treatment period begins on the day the subject receives the first dose of study drug through the point at which the principal investigator determines the subject will be permanently discontinued from study drug. Dates for subsequent study visits will be determined based upon this day and should occur within ± 3 days of the scheduled date unless delayed for safety reasons. During the Day 1 visit, results from screening visit evaluations should be reviewed to determine whether the subject continues to meet the eligibility requirements as specified in the Protocol.

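### Sections 6.1, 6.2 and 5.4.1 leave room to judge eligibility after open-label allocation and to withdraw a randomised patient from the study case by case, which puts the Day 28 response at risk of arm-dependent missingness

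*Protocol*

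**What the plan says.** Section 4.4 gives an order. Site staff determine eligibility, and after that: "Then, the participants who meet the enrollment criteria will be randomized to receive one of the two treatments in a 1:1 ratio". The same section states that "Treatment allocations are not masked to investigators or participants as CSA and methylprednisolone dosage are different between the two groups".

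Section 6.1 is less strict on timing: "Results from the screening visit evaluations will be reviewed to confirm subject eligibility before randomization or the administration of study drug". It ends screening on the day the patient is "randomized in the study (Day 1). The screening period may not exceed 2 days", and adds: "Treatment should start as soon as possible but within 1 days after the date of randomization".

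Section 6.2, on the treatment period, calls for a further check on Day 1 in these terms: "results from screening visit evaluations should be reviewed to determine whether the subject continues to meet the eligibility requirements as specified in the Protocol".

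Section 5.4.1 covers a patient found during the study not to have met the criteria: "then the medical monitor, in collaboration with the investigator, will determine whether the subject should be withdrawn from the study". The list holding that sentence is introduced as reasons why a patient may be withdrawn from study treatment.

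Section 8.4 includes all randomised participants in the primary analysis of all outcomes, and the synopsis bases all analyses on the intention-to-treat set.

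**The concern.** In an open-label trial, the main protection against selection after randomisation is that eligibility is settled before anyone at the site knows the arm. Section 4.4 provides this. Section 6.1 weakens it by offering a second, later deadline, and section 6.2 adds a review on the randomisation day whose place in the sequence is not fixed.

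Some criteria in section 3.2 rest on judgement. The clearest is exclusion 12, poor compliance in the view of the research team; vital organ dysfunction (exclusion 5) is another. Such a criterion can be read differently once the arm is known. Section 5.4.1 sets no rule for the decision that follows and does not ask that it be made without knowledge of the arm.

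What is at stake is the primary endpoint. If a patient leaves the study shortly after randomisation, Day 28 response may not be recorded, and the chance of that could differ between arms.

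**Working it through.** The point carries no figure of its own, so the check is mainly a reading of the sections side by side.

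**1. Can eligibility be judged after allocation?**
- Section 4.4: eligibility first, then randomisation.
- Section 6.1: confirmation before randomisation or before dosing. Dosing may come up to 1 day after randomisation, so the second alternative permits confirmation once the arm is known.
- Section 6.2: a review on Day 1. Section 6.1 defines Day 1 as the randomisation day. No section says whether the review comes before or after allocation.
- Result: section 6.1 allows it, section 6.2 is ambiguous, and section 4.4 points the other way.

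**2. Which criteria are exposed?**
- For repeated screening tests, section 6.1 uses the most recent result before randomisation. Section 6.2 reviews screening results and does not call for new tests.
- Result: a blood count that changes after randomisation is not an eligibility input under these sections. The exposure lies mainly in judgement-based criteria such as exclusion 12.

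**3. What happens to a patient then judged ineligible?**
- Section 5.4: stopping study treatment is not study completion, and follow-up begins.
- Section 5.4.1: the decision is worded as leaving the study, in a list about leaving treatment.
- Section 5.4.2: permanent discontinuation of study drug means withdrawal from the study, with an end-of-treatment visit. The same section also lets patients stop treatment and stay in follow-up.
- Result: the three sections conflict.

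**4. Is Day 28 still assessed?**
- Section 7.5.1 first sets weekly grading for 8 weeks after randomisation, that is to Day 56, which covers Day 28.
- It then says that patients who withdrew for reasons other than GVHD progression are staged at the safety follow-up visit and every 28 days thereafter. Section 6.5.1 puts that visit 180 days after the end-of-treatment visit.
- For an end-of-treatment visit on Day 1, the next staging is at about Day 1 + 180 = Day 181, which is 181 − 28 = 153 days after Day 28. Section 4.6 gives a safety follow-up of 365 days instead, which is later still.
- Result: on one of two available readings, Day 28 is not assessed.

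**5. How would a missing Day 28 response be treated?**
- Section 8.4 keeps the patient in the analysis. It expects under 10% missing, and says multiple imputation and best-case/worst-case analyses should be considered if ignoring the missing data is not plausible.
- Result: the patient is in the set, but this section supplies no outcome for that patient unless that condition is met.

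**6. Does the sample size absorb it?**
- Inputs from section 8.1: 55% versus 75%, two-sided 5%, power 80%, 10% withdrawal. The mean proportion is 0.65.
- n per arm = [1.960 × √(2 × 0.65 × 0.35) + 0.842 × √(0.55 × 0.45 + 0.75 × 0.25)]² / 0.20² = (1.322 + 0.555)² / 0.04 ≈ 88.1, rounded up to 89.
- 89 / 0.90 = 98.9, rounded up to 99 per arm, or 198 in total. The plan's figure is reproduced.
- The allowance covers lost precision. It gives no protection if losses depend on arm.

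**The case against.** The strongest reply is that section 4.4 already fixes the order, with a web system independent of the sites, and that the Day 1 review can be read as the last check before randomisation. That reading is available, and for section 6.2 it may well be the intended one. It does not remove the second alternative in section 6.1.

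A reader might infer that the protocol lets patients be dropped from the analysis by arm, and might try to size this by removing some non-responders from the ruxolitinib denominator. The documents do not support that. Section 8.4 and the synopsis keep all randomised participants. The number removed, the one-sidedness and the assumption that those removed are non-responders would all have to be invented. The direction could equally be the reverse. If a missing response is counted as non-response, which the statistical analysis plan may state, the denominator does not change at all.

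The section 5.4.1 clause is permissive, applies to both arms and involves the medical monitor as well as the investigator. That is correct, and it lowers the risk. But no section says the medical monitor is masked, and the masking in section 4.4 covers outcome assessment and data analysis, not eligibility decisions.

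The conflict between leaving treatment and leaving the study affects every discontinuation, not only those for ineligibility. That also stands; it is a reason to settle the conflict once, for all cases. Not replacing patients (section 4.5.3) does not make the problem worse.

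**Conclusion.** The point holds in a limited form. The protocol contradicts itself on whether eligibility is settled before open-label allocation, and on whether a patient found ineligible leaves treatment or leaves the study. The consequence is possible arm-dependent loss of the Day 28 response, not exclusion from the analysis set.

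The size and direction of any bias cannot be derived from the documents, because they do not say how many patients would be affected, in which arm, or with what response. The conclusion rests on two readings: that the second alternative in section 6.1 means what it says, and that the later paragraph of section 7.5.1 governs a patient withdrawn for ineligibility. If weekly grading continues for such patients, Day 28 is captured and little remains beyond the wording. The sample size is not affected. The changes are worth making because they cost almost nothing and close the gap on either reading.

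**What to change.** - **Section 6.1:** delete the alternative that refers to study drug administration, so that eligibility is confirmed before randomisation only, in line with section 4.4.
- **Section 6.2:** state that the Day 1 eligibility review is completed before the allocation is released.
- **Section 5.4.1:** replace withdrawal from the study with withdrawal from study treatment in the ineligibility clause. State that a randomised patient later found ineligible stays in the intention-to-treat set and keeps all scheduled GVHD assessments, including Day 28, and survival follow-up, unless consent is withdrawn.
- **Sections 5.4, 5.4.1 and 5.4.2:** reconcile them on leaving treatment versus leaving the study, and align section 7.5.1 so that staging after withdrawal does not skip Day 28.

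Whether such a patient continues study treatment remains a clinical decision that these changes do not touch. The cost is a protocol wording amendment, with no additional patients and no visits beyond those already scheduled.

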## 6.2. Treatment

The treatment period begins on the day the subject receives the first dose of study drug through the point at which the principal investigator determines the subject will be permanently discontinued from study drug. Dates for subsequent study visits will be determined based upon this day and should occur within ± 3 days of the scheduled date unless delayed for safety reasons. During the Day 1 visit, results from screening visit evaluations should be reviewed to determine whether the subject continues to meet the eligibility requirements as specified in the Protocol.

## 6.3. End of Treatment

If a decision is made that the subject will permanently discontinue study treatment, the EOT visit should be conducted. If the EOT visit coincides with a regular study visit, the EOT evaluations will supersede those of that scheduled visit, and the data should be entered in the EOT visit in the eCRF. The subject should be encouraged to return for the follow-up visit.

## 6.4. Re-Treatment

For subjects who experience acute GVHD recurrence after taper of randomized treatment is completed, investigators have the option to use open-label ruxolitinib plus corticosteroids for the treatment of recurrent acute GVHD irrespective of initial randomized treatment. For the purpose of this Protocol, treatment of recurrent acute GVHD with open-label ruxolitinib plus corticosteroids will be called the re-treatment phase. Subjects entering the re-treatment phase will be required to follow the assessment schedule. Corticosteroid tapering will be performed

at the investigator's discretion. Investigators wishing to initiate a taper of ruxolitinib earlier than Day 180 may do so upon consultation with and approval from the sponsor's medical monitor. Subjects may be re-treated with ruxolitinib only once. Subjects ending the re-treatment phase will repeat the EOT visit and subsequent safety and survival follow-up visits.

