| \| **Primary Objective** \| **Primary Endpoint** \| \| --- \| --- \| \| Compare the efficacy of ruxolitinib in combination with corticosteroids versus corticosteroids in terms of overall response rate (ORR) at Day 28 in subjects with acute graft-versus-host disease (acute GVHD). \| ORR at Day28, defined as the proportion of participants demonstrating a complete response (CR), or partial response (PR) \| \| **Secondary Objective** \| **Secondary Endpoints** \| \| Compare additional response and longer-term efficacy outcomes between treatment cohorts. \| Durable ORR at Day56, defined as the proportion of patients in each arm whose response on day 28 lasts until day 56 after randomization. \| \| DOR at Month 6 for responders will be calculated. The DOR is defined from the time of the onset of response to loss of response. Subjects who died or discontinued will be censored at the  death date or the previous assessment. \| \| Response duration, defined as the time from the first response to the first recurrence/progression of acute GVHD or additional immunosuppressants for GVHD. \| \| NRM at Month 24, defined as the time from enrollment to death due to any causes other than hematologic disease relapse. \| \| Cumulative incidence of relapse (CIR) at Month 24, defined as the proportion of subjects whose underlying hematologic disease relapses. \| \| Disease-free survival (DFS) at Month 24, defined as the time from enrollment to relapse of primary disease or death from any causes, whichever occurred first. \| \| Failure-free survival (FFS) at Month 24, defined as the time from randomization to disease relapse or progression, non-relapse mortality, or the addition of new therapy for acute GVHD. \| \| Overall survival (OS) at Month 24, defined as the time from randomization to death due to any causes. \| \| Assess the incidence and severity of adverse events (AEs) and serious adverse events. \| Clinical safety data (eg, AEs, infections) will be tabulated and listed. \| \| Evaluate the use and discontinuation of  corticosteroids. \| Average and cumulative corticosteroid dose at Days 365; \| \| Evaluate the use and discontinuation of  immunosuppressive medications. \| Proportion of subjects who discontinue immunosuppressive medications at Days365. \| \| Evaluate the incidence of recurrent acute GVHD \| Incidence rate of recurrent acute GVHD through Month 24. \| \| Evaluate the incidence of cGVHD. \| Incidence rate of cGVHD at Month 24. \| \| **Overall Study Design:**  This trial is an open-label, multicenter, prospective randomized two-arm phase II study comparing the efficacy and safety of ruxolitinib plus methylprednisolone (1 mg/kg) vs. methylprednisolone (2 mg/kg) alone. The biomarkers of acute GVHD, such as sST2, sTNFR1, IL-6, IL-8, and REG3α will be tested at acute GVHD onset. Patients with newly diagnosed intermediate-risk or high-risk acute GVHD, as defined by Minnesota acute GVHD risk score and the biomarker score will be included. The treatment efficacy will be evaluated with respect to the level of biomarkers and clinical manifestations. Written informed consent must be obtained from the patients before enrollment in the study. The consent form and related materials are available from the corresponding author on request.  **Study Population:**  Eligible patients with intermediate-risk or high-risk acute GVHD graded according to the modified Glucksberg criteria, Minnesota acute GVHD risk score and the biomarker score and untreated with systemic acute GVHD therapy will be enrolled in this study.  **Key Inclusion Criteria:**   - Male or female, 14 to 65 years old. - Have undergone first allogeneic hematopoietic stem cell transplantation (allo-HSCT) from any donor source using bone marrow, peripheral blood stem cells, or cord blood for hematologic malignancies. - Develop a de novo acute GVHD, defined as intermediate- or high-risk using the Minnesota acute GVHD risk score and MAGIC biomarker algorithm.   **Key Exclusion Criteria:**   - Has received more than one allogeneic stem cell transplant. - Female patients with pregnant or breast-feeding. - Has Acquired Immune Deficiency Syndrome (AIDS), or hepatitis B/C infection, uncontrolled bacterial, fungal, or viral infections. - Allergies to ruxolitinib. - Vital organ dysfunction unrelated to GVHD, including persistent bilirubin abnormalities or severe heart and respiratory diseases. - Relapse of the primary disease or graft rejection after transplantation. - Presence of GVHD overlap syndrome. - Presence of cGVHD or associated clinical signs or DLI-induced acute GVHD or interferon. - Previous history of JAK1/2 inhibitor treatment after transplantation, except JAK inhibitors administered before the transplantation. - absolute neutrophil count (ANC) <0.5×10^9^/L or platelet count (PLT) < 20×10^9^/L - Serum creatinine > 2.0 mg/dL or creatinine clearance < 40 mL/min measured or calculated by Cockroft-Gault equation. - Patients with poor compliance should not be included in the study based on the judgment of the research team, for example if they refused to take medicine at will many times during the previous treatment.   **Study Drug, Dosage, and Mode of Administration:**  **Ruxolitinib plus corticosteroids treatment (ruxolitinib group):**  The initial dose of methylprednisolone is 1 mg/kg/day intravenously given in this arm for at least 7 days. The dosage of ruxolitinib is 5 mg PO QD. CSA will be administered intravenously at a dose of 2 mg/kg twice daily, targeting minimum concentration levels of 150–250 ng/mL. If GVHD response to treatment is assessed as PR/CR at 7 days, methylprednisolone will be tapered, followed by reduction and discontinuation of CSA and then ruxolitinib. The reduction of the methylprednisolone in the ruxolitinib group is gradual, suggesting it be tapered off over 6 weeks as follows: dosage reduced to 0.6 mg/kg/day, 0.4 mg/kg/day, 0.3 mg/kg/day, 0.25 mg/kg/day, and 0.18 mg/kg every 5 days, followed by 0.1 mg/kg/day at week 4, 0.1 mg/kg every other day after 5 days and stopped at week 6. After steroid discontinuation and CR or stable PR maintained for 6 weeks, CSA is tapered over 60 days. After CSA discontinuation and no presence of recurrent GVHD, ruxolitinib is tapered off over 90 days, which is totally maintained for approximately 6 months.  **Corticosteroid treatment (corticosteroids group):**  The initial dose of methylprednisolone is 2 mg/kg/day given twice daily for at least 7 days and then reduced. The dosage of methylprednisolone in the corticosteroids group is decreased gradually after CR and tapered off over 10 weeks as the following: dosage reduced to 1 mg/kg/day to 0.6 mg/kg/day, 0.4 mg/kg/day, 0.3 mg/kg/day, 0.25 mg/kg/day, and 0.18 mg/kg every 7 days, and then 0.1 mg/kg/day at week 4, 0.1 mg/kg every other day after 5 days, and stopped at week 10. CsA was administered intravenously at a dose of 2 mg/kg twice daily, targeting minimum concentration levels of 150–250 ng/mL. The recommended duration of CsA is 6 months.  In both arms, for refractory acute GVHD, i.e., the progression of GVHD after 3 days of therapy, no improvement within 7 days, or no CR after 14 days of therapy, the second-line therapy will be started. For refractory acute GVHD or recurrent acute GVHD, basiliximab may be used as second-line therapy, and other alternative drugs included methotrexate or mesenchymal stem cells may be used at the researcher’s decision. For refractory acute GVHD, methylprednisolone is discontinued and CsA is continued in both arms. Prolonged maintenance of ruxolitinib is used in the ruxolitinib group. A standardized follow-up booklet is given to each enrolled patient for recording the dose, frequency, and administration method of the drugs. **Estimated Duration of Participation:** Subject participation is expected to average 24 months, which includes the following:   - A screening period lasting up to 28 days. - A treatment period lasting as long as the subject is benefiting from treatment. - A safety follow-up period lasting 180 days after treatment ends. - A survival follow-up period lasting until death or study withdrawal. \| \| \| **Estimated Number of Subjects:** 198 subjects. \| \| \| **Principal Coordinating Investigator:** [name] \| \| \| **Statistical Methods:**  The sample size is calculated according to the primary endpoint (ORR) of the study. Based on our published phase I study of 32 acute GVHD patients who received steroids as first-line therapy, an expected proportion of 55% for the patients treated with corticosteroids only was established. Based on our published data of patients with acute GVHD grade I–IV who received steroid-ruxolitinib (5 mg/day) as first-line therapy, the ORR was 82.05%. Patients with acute GVHD grade I were also included in the phase I analysis. Thus, an expected proportion of 75% for the patients treated with steroid-ruxolitinib (5mg/day) was established. This study is planned to detect a response difference between treatment arms at a two-sided significance level α=5% with a power of 1-β=80%. The sample size was estimated using PASS software based on the primary endpoint (ORR). Allowing a withdrawal rate of 10%, 198 patients (99/group) will be required.  Continuous data are described as median with interquartile range (IQR) or mean and standard deviation (SD) according to the normality of distribution. The categorical data are described as n (%). The ORR was calculated with its 95% confidence interval (CI) and compared by the stratified Cochran–Mantel–Haenszel test. Additionally, a logistic regression model, which included aGVHD risk (high vs. intermediate), and disease status before transplantation (CR vs. no CR) as covariates, was established to explore the association between treatment and ORR on day 28. Post-hoc subgroup analysis was performed by biomarker risk, age and GVHD grade, although these were not prespecified in the protocol. The cumulative incidence of recurrent aGVHD was analysed using the Fine and Gray test in a competing risk framework. The Kaplan–Meier method was used to estimate the ORR on day 56, OS, DFS, and FFS, and the log-rank test was used to evaluate the difference between the groups. The cumulative incidence rates of NRM and relapse were estimated using a competing risk model and compared using the Fine and Gray test. A Cox proportional hazard regression model was used for multivariable regression analysis for OS and DFS. Multivariable regression analysis was performed for NRM using the Fine–Gray proportional hazard regression for competing events. The following variables were included in the univariable analysis: primary disease, cytogenetic risk, age and gender of the donor and recipient, source of graft, treatment arm, aGVHD risk, and disease status before transplantation. Variables with P<0.1 in univariate analysis or variables known to influence the outcomes were included in the multivariable analysis. Competing events were defined as follows: for GVHD, death without the event; for relapse, death without relapse; and for NRM, relapse. Any difference for which the two-sided P<0.05 was considered statistically significant. All analyses were carried out using SPSS 22.0 software (IBM Corporation, Armonk, NY, USA) or R version 4.1.2 (www.cran.r-project.org). All statistical analyses were based on the intend to treat set. \| \| | |

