### 5.1.2. Corticosteroids (Corticosteroids Group)

**5.1.2.1. Administration and Tapering**

The initial dose of methylprednisolone is 2 mg/kg/day given twice daily for at least 7 days and then reduced ^[8]^. The dosage of methylprednisolone in the corticosteroids group is decreased gradually after CR and tapered off over 10 weeks as the following: dosage reduced to 1 mg/kg/day to 0.6 mg/kg/day, 0.4 mg/kg/day, 0.3 mg/kg/day, 0.25 mg/kg/day, and 0.18 mg/kg every 7 days, and then 0.1 mg/kg/day at week 4, 0.1 mg/kg every other day after 5 days, and stopped at week 10. CsA was administered intravenously at a dose of 2 mg/kg twice daily, targeting minimum concentration levels of 150–250 ng/mL. The recommended duration of CsA is 6 months.

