### 8.3.3. Safety Analyses

A TEAE is either an AE reported for the first time or worsening of a pre-existing condition after first dose of study drug. Analysis of AEs will be limited to TEAEs, but data listings will include all AEs, regardless of their timing to study drug administration. Severity of AEs will be based on NCI CTCAE v4.0.

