## 8.4. Handling of missing data

All randomized participants will be included in the primary analysis of all outcomes. The proportion of missing values on the primary and secondary outcomes would be <10%. Thus, a secondary analysis should be considered using multiple imputations and present best-case/worst-case scenarios if ignoring the missing data is not plausible.

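### Adverse events during open-label ruxolitinib re-treatment are pooled with randomised-phase events, so the by-arm safety table mixes exposures

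*Protocol*

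**What the plan says.** **Re-treatment.** Section 6.4 of the protocol covers this group: "For subjects who experience acute GVHD recurrence after taper of randomized treatment is completed". For them, "investigators have the option to use open-label ruxolitinib plus corticosteroids for the treatment of recurrent acute GVHD irrespective of initial randomized treatment". The phase has a name, follows the assessment schedule, and ends with a second round of visits: "Subjects ending the re-treatment phase will repeat the EOT visit and subsequent safety and survival follow-up visits". Safety data from re-treatment are therefore collected in both arms.

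**Safety analysis.** Section 8.3.3 gives the definition: "A TEAE is either an AE reported for the first time or worsening of a pre-existing condition after first dose of study drug". It continues: "Analysis of AEs will be limited to TEAEs, but data listings will include all AEs, regardless of their timing to study drug administration". The window has a start and no end, and re-treatment is not mentioned. Corticosteroids are listed among the study drugs in section 5.1, so in a control patient the window opens with the first steroid dose. Section 7.4.1.2 adds that an event whose severity changes is analysed once, at its highest grade.

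**Grouping.** The Statistical Methods part of the Synopsis closes with "All statistical analyses were based on the intend to treat set". Section 8.4 states: "All randomized participants will be included in the primary analysis of all outcomes". The protocol names no safety set, no grouping by treatment received and no separate table for the re-treatment phase.

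**The concern.** Incidence and severity of adverse events is a stated secondary objective (section 2), and section 1.4 names infection and myelosuppression as the risks to watch with ruxolitinib. A by-arm table serves that objective only if each column reflects the regimen at its head.

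Under the rules above, a control patient who starts ruxolitinib after recurrence and then has a cytopenia or an infection is counted under corticosteroids. A ruxolitinib-arm patient who recurs and is re-treated has a second course counted with the first. Neither column then describes the randomised regimen alone, and a reader of the table cannot separate the two phases.

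**Working it through.** **1. Denominator.** The plan's 99 per arm reproduces. For 55% vs 75%, two-sided 5%, 80% power, pooled variance:

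n = [1.960 × √(2 × 0.65 × 0.35) + 0.842 × √(0.55 × 0.45 + 0.75 × 0.25)]² / 0.20² = 88.1, rounded up to 89; 89 / 0.90 = 98.9, rounded up to 99.

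This point does not dispute that figure. It only supplies the denominator.

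**2. Timing.** The control steroid dose is "decreased gradually after CR and tapered off over 10 weeks" (section 5.1.2.1). Re-treatment requires a completed taper, so it falls after Day 28 and cannot alter the primary endpoint.

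**3. Dilution from control crossover.** Let p_C and p_R be the risks of a given event on each randomised regimen, and f the share of controls re-treated. Assume a re-treated control ends with risk p_R.

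- Reported control risk = p_C + f × (p_R − p_C)
- Reported difference = (1 − f) × (p_R − p_C)
- Control patients with an event added = 99 × f × (p_R − p_C)

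The document does not give p_C and p_R for this setting. Two assumed pairs show the range:

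| f | Controls re-treated of 99 | Difference, 20% vs 40% | Added | Difference, 10% vs 26% | Added |
|---|---|---|---|---|---|
| 0 | 0 | 20.0 points | 0 | 16.0 points | 0 |
| 10% | 9.9 | 18.0 | 2.0 | 14.4 | 1.6 |
| 20% | 19.8 | 16.0 | 4.0 | 12.8 | 3.2 |
| 31.2% | 30.9 | 13.8 | 6.2 | 11.0 | 4.9 |
| 40% | 39.6 | 12.0 | 7.9 | 9.6 | 6.3 |

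With the grade 3 infection figures in section 1.3 (22% vs 19%, in steroid-refractory patients), the excess is 3 points. It falls to 2.7 at f = 10% and to 3 × 0.688 = 2.1 at f = 31.2%.

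**4. What f might be.** The only recurrence figure is 31.2% (10 of 32) in section 1.3, from patients given ruxolitinib. Applied to all controls it gives 0.312 × 99 = 30.9. Applied only to the planned responders it gives 0.55 × 99 = 54.5, and 0.312 × 54.5 = 17, so f = 17/99 = 17%. Not every recurrence follows a completed taper, re-treatment is optional, and the Synopsis also names other second-line drugs for recurrence. The true f could be anywhere from zero up to these values.

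**5. Re-treatment in the ruxolitinib arm.** Let g be the share re-treated there and e_R the added risk per re-treated patient. Then reported difference = (1 − f) × (p_R − p_C) + g × e_R.

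In the 20% vs 40% case, the chance that a course adds an event in someone still event-free is 1 − 0.60/0.80 = 0.25. If a second course acts the same way, e_R = 0.60 × 0.25 = 0.15. Starting from 20 points:

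- f = 10%, g = 10%: 20 − 2.0 + 1.5 = 19.5
- f = 20%, g = 10%: 20 − 4.0 + 1.5 = 17.5
- f = 10%, g = 20%: 20 − 2.0 + 3.0 = 21.0

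The sign of the net distortion depends on f and g, and the protocol gives neither.

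**The case against.** **This belongs in the SAP.** Section 8.3.3 is three sentences, and window ends, safety sets and re-treatment tables are commonly settled later. That would answer a complaint about silence. Here the protocol itself states a treatment-emergent rule with no end and a rule for all statistical analyses. A SAP that followed both would inherit the pooling.

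**The intention-to-treat sentence was meant for efficacy.** It closes a paragraph that never mentions adverse events, and section 8.4 concerns missing data. This is fair: applying it to the safety table rests on its literal scope. It is also why narrowing the sentence is a sufficient remedy for that part.

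**The phases are already separable.** Re-treatment is a named phase with its own visits, reporting limits exist around 30 days after the last dose and at the follow-up visit, and causality of serious events is recorded per drug. These help a listing, but they govern collection. They do not change the column in which an event is counted.

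**A whole-strategy table is legitimate, and a cut-off removes a selected group.** Both stand, and both argue for keeping a whole-period table as support.

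**Stronger readings that the protocol does not support:**

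- A reader might infer that ruxolitinib toxicity is certain to be hidden. Step 5 shows that the net direction is open.
- A reader might multiply the 26% cytomegalovirus reactivation in section 1.3 by 10 to 30 assumed crossovers and report 0.26 × 10 = 2.6 to 0.26 × 30 = 7.8 misplaced events. That is a gross count with no background risk. It takes the 26% from steroid-refractory patients, and the top of the range leans on recurrence in ruxolitinib-treated patients. With an assumed 10% background the net is 0.16 × 10 = 1.6 to 0.16 × 30 = 4.8. Section 1.3 also reports similar infection incidence between arms in the steroid-refractory trial, and less reactivation at the 5 mg daily dose.
- A reader might speak of lost power for safety. No between-arm safety test is planned; the data are to be tabulated and listed.

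**Conclusion.** The point holds as a defect in how the safety table is defined. Taken literally, the protocol pools re-treatment events with randomised-phase events and counts ruxolitinib-phase events in re-treated controls under corticosteroids.

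Control crossover alone shrinks a true ruxolitinib excess to (1 − f) of its size, for example from an assumed 20 points to between 18.0 and 13.8 for f between 10% and 31.2%. This assumes that a re-treated control takes on the full ruxolitinib-arm risk and that the Synopsis sentence covers safety. Re-treatment in the ruxolitinib arm offsets or reverses this, so neither the net size nor its sign can be stated from the document.

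The Day 28 response endpoint is untouched, and intention-to-treat remains right for efficacy. The point is worth correcting because the remedy is cheap and the table is the main evidence for a stated objective.

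**What to change.** The changes concern analysis only; the re-treatment option itself stays as it is.

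1. In section 8.3.3, end the comparative treatment-emergent window at the first dose of re-treatment, or at a stated time after the last randomised dose if that comes earlier.
2. Tabulate re-treatment-phase events in a separate table by initial arm, with the number re-treated in each arm.
3. Give exposure-adjusted rates beside the incidences, because the cut-off makes follow-up unequal between patients and possibly between arms.
4. Limit the Synopsis intention-to-treat sentence to efficacy analyses, and state the safety set and its grouping in section 8.3.3. An as-treated set defined by first treatment received would not be enough on its own: crossover controls would stay in the control column. The window does the work.
5. Keep a whole-period table by randomised arm as supportive.

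The cost is wording and one extra table. The main comparison loses events after recurrence, and the patients cut off are a selected group, which the supportive table makes visible. No patients or visits are added. Event dates (section 7.4.1.2), medication changes (section 7.3), and new GVHD therapies and ruxolitinib dosing (Appendix A) are already recorded.
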